## Abstract

**Background:**

Depression is a global health challenge. Although there are effective psychological and pharmaceutical interventions, our best treatments achieve remission rates less than 1/3 and limited sustained recovery. Underpinning this efficacy gap is limited understanding of how complex psychological interventions for depression work. Recent reviews have argued that the active ingredients of therapy need to be identified so that therapy can be made briefer, more potent, and to improve scalability. This in turn requires the use of rigorous study designs that test the presence or absence of individual therapeutic elements, rather than standard comparative randomised controlled trials. One such approach is the Multiphase Optimization Strategy, which uses efficient experimentation such as factorial designs to identify active factors in complex interventions. This approach has been successfully applied to behavioural health but not yet to mental health interventions.

**Methods/Design:**

A Phase III randomised, single-blind balanced fractional factorial trial, based in England and conducted on the internet, randomized at the level of the patient, will investigate the active ingredients of internet cognitive-behavioural therapy (CBT) for depression. Adults with depression (operationalized as PHQ-9 score ≥ 10), recruited directly from the internet and from an UK National Health Service Improving Access to Psychological Therapies service, will be randomized across seven experimental factors, each reflecting the presence versus absence of specific treatment components (activity scheduling, functional analysis, thought challenging, relaxation, concreteness training, absorption, self-compassion training) using a 32-condition balanced fractional factorial design (2_IV_
^7-2^). The primary outcome is symptoms of depression (PHQ-9) at 12 weeks. Secondary outcomes include symptoms of anxiety and process measures related to hypothesized mechanisms.

**Discussion:**

Better understanding of the active ingredients of efficacious therapies, such as CBT, is necessary in order to improve and further disseminate these interventions. This study is the first application of a component selection experiment to psychological interventions in depression and will enable us to determine the main effect of each treatment component and its relative efficacy, and cast light on underlying mechanisms, so that we can systematically enhance internet CBT.

**Trial registration:**

Current Controlled Trials ISRCTN24117387. Registered 26 August 2014

**Electronic supplementary material:**

The online version of this article (doi:10.1186/s12888-016-1054-8) contains supplementary material, which is available to authorized users.

## Background

Depression is a major global health challenge [1, 2]: it is highly prevalent, recurrent [3] and a leading cause of disability worldwide, with enormous individual, societal, and economic burden [4]. Although both antidepressant medication and cognitive-behavioural therapy (CBT) are evidence-based and recommended treatments for depression, there is still a major treatment gap. First, even these, our best treatments, only achieve remission rates of less than 1/3 and limited sustained recovery (50–80 % relapse/recurrence) [5] (an *efficacy gap*). Second, there is sub-optimal adherence to antidepressants and patients express a preference for psychological interventions (a *preference gap*). Third, traditional face-to-face psychotherapy can never be sufficiently widely available to reduce the global burden of depression, indicating the need for alternative delivery methods [5, 6] (a *scalability gap*).

One solution to address the scalability gap is via internet-based or e-therapy. Internet-CBT for depression has comparable efficacy to face-to-face treatment when supported by a therapist [7], can increase access by removing time constraints and geographical restrictions to attending therapy [7], and can increase cost-effectiveness and treatment coverage [8] by reducing therapist treatment time. Effective unguided e-therapy would have almost no constraints on volume of use and would be globally scalable and accessible.

Underpinning the efficacy gap is limited understanding of how complex psychological interventions for depression work. Resolving the active mechanisms of psychological interventions has been identified as a major priority [5, 9–11]. Uncovering the mechanisms of psychological treatments and optimising the content and delivery of treatments is necessary to build more potent, scalable, and efficient treatments. Because little progress has been made in specifying the active ingredients of CBT for depression [5, 9, 10], there have been no significant gains in the effectiveness of CBT for depression for over 30 years. Recent reviews have argued that we need to identify active elements so that therapy can be parsed and distilled to focus on what is essential and most engaging to patients, making it briefer, more potent, and facilitating wider dissemination and coverage [11, 12]. The Institute of Medicine recently proposed that determination of which elements are critical depends on testing the presence or absence of individual therapeutic elements in rigorous study designs [12].

One reason for limited progress in understanding mechanisms is the overreliance on parallel group comparative randomised controlled trials (RCTs). Such RCTs are effective for establishing the relative efficacy of one treatment intervention versus another, where they provide the gold standard for determining if an intervention works. However, they are limited at investigating the specific mechanisms of how interventions work because they can only compare the overall effects of each intervention package. Psychological treatments such as CBT are complex interventions, typically made up of multiple elements and components, each of which potentially acts via distinct mechanisms.

In standard comparative RCTs, all treatment components and their closely related hypothetical mechanisms are aggregated and confounded together in the comparison of treatment conditions. As a consequence, this design is unable to test specific main effects of treatment components and any possible synergistic or antagonistic interactions between individual treatment components, limiting advances in mechanistic understanding. If an RCT finds one treatment better than another, we don’t know which components made a difference; if there is no difference, we don’t know whether there are any components that effected an improvement.

Instead, we propose an innovative approach to begin to address both the scalability and efficacy gaps by using a fractional factorial design for the first time to identify the active ingredients within internet-delivered CBT for depression (the IMPROVE-2 study; Implementing Multifactorial Psychotherapy Research in Online Virtual Environments). This approach directly responds to the Institute of Medicine’s (2015) call for rigorous trial design to disentangle specific therapy elements.

Our approach is a theory-driven component selection experiment framed within the Multiphase Optimization Strategy (MOST) [13–19] approach. MOST, rooted in engineering, agriculture, and behavioural science, is a principled and comprehensive framework for optimizing and evaluating behavioural interventions [13–15].

The optimization phase of MOST uses efficient experimentation to identify which of a set of candidate components is effective and should be included in the optimized intervention. Although a wide variety of experimental designs are possible candidates for use in the optimization phase, frequently factorial or fractional factorial designs emerge as most efficient [14, 15, 20]. Factorial and fractional factorial experiments allow one to explore main effects of factors and interactions among factors [20]. A fractional factorial design is a variation on the factorial design that employs a systematic approach to reduce the number of experimental conditions to allow a more manageable study, at the cost of allowing only main effects and a pre-specified set of interactions to be tested. Fractional factorial designs require the assumption that higher-order interactions are negligible in size, because they are combined, or aliased, with lower-order effects. In the evaluation phase of MOST, the optimized intervention, constructed based on the findings from the optimization phase and assembled to meet a specific optimization criterion, is compared against a control intervention in a standard RCT.

Critically, the optimization phase proposed by MOST [13] provides direct evidence about the effects and interactions of individual components within a treatment package, which is necessary for methodically enhancing and simplifying complex interventions [21]. This approach enables us to develop a mechanistic understanding of therapy and to select active and reject inactive/counter-productive components or elements.

MOST is well-validated [13, 22–25] and recommended within the Medical Research Council Complex Intervention guidelines [26]. A key advantage is greater experimental efficiency, with a focus on identifying “active ingredients” versus “inactive” or extraneous components before moving onto large-scale comparative trials, resulting in fewer overall resources required to answer the research questions in the long run than with the traditional approach [27]. However, to date, MOST has not been applied to psychological interventions for mental health.

In the current study, we therefore will combine the MOST approach with an e-health delivery format for CBT to build in treatment reach, scalability, and increased treatment coverage for the optimised treatment from the beginning [6], as the goal is to develop an optimised scalable evidence-based treatment. In addition, internet-delivered therapy has the major advantage that treatment content can be standardised and fixed, and written therapist responses can be closely demarcated, reducing unwanted “drift” from treatment protocols [7]. This helps prevent potential contamination between different treatment components, an essential condition for a factorial design.

Consistent with the MOST framework, we chose the treatment components to ensure that they are conceptually and operationally distinct from each other, so that each can be evaluated independently. This does not mean that we assume that the treatment components do not interact; we will use the factorial approach with effect coding as this allows us to concurrently test both main effects and interactions [14, 17]. The current design assesses the effectiveness of seven treatment components from standard CBT [28] and recent treatment innovations derived from experimental research [29, 30], with each hypothesized to specifically target distinct mechanisms arising from different theoretical models. We will use a fractional factorial design to retain the benefits of a factorial design whilst making the study more logistically manageable and feasible to deliver: the fractional factorial design reduces the total number of conditions from 128 to 32.

IMPROVE-2 builds on a previous feasibility study (IMPROVE-1), which assessed the feasibility of online recruitment of patients with depression, of maintaining treatment integrity and fidelity across randomisation into multiple treatment conditions and of avoiding contamination across treatment conditions, and assessed rates of attrition and retention and treatment adherence ([name], [name], [name], [name], [name], [name], [name] & [name]. Implementing multifactorial psychotherapy research in online virtual environments (IMPROVE-1): a feasibility trial of the MOST component selection experiment for internet cognitive-behavioural therapy for depression, In preparation). IMPROVE 1 demonstrated that this approach was feasible, and that it was possible to randomize individuals into multiple treatment conditions (32 in the fractional factorial design) without any contamination and with 100 % fidelity for the interventions received. However, IMPROVE-1 was not powered to test main effects and interactions for each of the seven experimental intervention factors on change in depression symptoms.

### Aims and objectives

The primary aim of this phase III trial is to test the main effects and selected interactions for seven treatment components within internet CBT for depression. The treatment components (in *italics*) and their associated hypothesized mechanisms-of-action are described below.

Within the behavioural model, *activity scheduling* and *absorption training* are hypothesized to increase response-contingent positive reinforcement [31] by respectively increasing frequency of positive reinforcement and direct contact with positive reinforcers. *Functional analysis* is proposed to target habitual avoidance and rumination by identifying antecedent cues, controlling exposure to these cues, and practising alternative responses to them [32].

Within the cognitive model, *thought challenging* is hypothesized to reduce the negative thinking characteristic of depression [28]. *Concreteness training* [30] is hypothesized to specifically reduce the overgeneralization cognitive bias identified as important in depression [33].

Further treatment components are hypothesized to improve emotional regulation. *Relaxation* is proposed to target physiological arousal and tension. *Self-compassion training* is proposed to activate the soothing and safeness emotional system, hypothesized to be downregulated in depression [34–36].

The use of a fractional factorial design will uniquely test hypotheses from different theoretical models concerning the mechanisms-of-action in internet CBT. By comparing the presence versus absence of each component, this factorial design can examine the main effect of each component on the primary outcome (e.g., testing whether thought challenging reduces symptoms of depression) and on secondary outcome measures indexing the specific mechanism theorised to be closely related to each component (e.g., testing whether thought challenging has a main effect on reducing self-reported negative cognition) and, whether this in turn mediates the effect of the treatment component on symptoms. Consistent with the Pareto principle and prior MOST studies [23], we predict that components and interactions will vary in treatment effect size, with many insignificant (i.e., not all components are active in therapeutic benefit of CBT). [name] and Nolen-Hoeksema (2014) predicted that treatment components that explicitly target depressogenic habits by identifying cueing stimuli and repeatedly training incompatible alternative responses (e.g., functional analysis) will have the largest sustained treatment effect [32].

A further advantage of a factorial design is that it provides a strong test of the relative contribution of specific versus non-specific common treatment factors. An important but as yet unresolved debate concerns the relative contribution of non-specific common factors shared across therapies (e.g., hope, remoralization, therapeutic alliance, treatment credibility) versus specific elements (e.g., reducing negative thinking, increasing behavioural activation). CBT includes generic therapy elements (e.g., providing a rationale, therapist support), and specific elements (e.g., activity scheduling, thought challenging), which are hypothesized to act through different mechanisms. Identifying the relative contribution of specific versus common factors has major theoretical and practical implications for therapy delivery. However, progress at disentangling specific from non-specific treatment effects has been limited because of difficulties in creating psychotherapy placebos (attentional controls) that match the genuine psychotherapy for credibility and structural equivalence [37]. In this factorial design, for any treatment component (e.g. relaxation), the aggregate of the 16 conditions where it is present (i.e., Table 1, conditions 17-32) are equivalent for treatment credibility, structure, delivery, rationale, therapist contact, and therapist allegiance with the aggregate of the 16 conditions where it is absent (i.e., Table 1, conditions 1–16). Hence, the evaluation of the main effect of relaxation involves the comparison of the average effect for the conditions where relaxation is present versus for the conditions where relaxation is absent. This design therefore provides an improved psychotherapy attentional control condition able to disentangle specific from non-specific common treatment factors. A significant main effect for any component would be evidence for a specific treatment effect within CBT for depression beyond non-specific common therapy factors.

**Table 1 Tab1:** Experimental groups of the fractional factorial design

Condition	Functional Analysis	Concrete training	Compassion	Absorption	Relaxation	Activity Scheduling	Thought Challenging
1	no	no	no	no	no	yes	yes
2	yes	no	no	no	no	no	no
3	no	no	yes	no	no	no	no
4	yes	no	yes	no	no	yes	yes
5	no	no	no	yes	no	yes	no
6	yes	no	no	yes	no	no	yes
7	no	no	yes	yes	no	no	yes
8	yes	no	yes	yes	no	yes	no
9	no	yes	no	no	no	no	no
10	yes	yes	no	no	no	yes	yes
11	no	yes	yes	no	no	yes	yes
12	yes	yes	yes	no	no	no	no
13	no	yes	no	yes	no	no	yes
14	yes	yes	no	yes	no	yes	no
15	no	yes	yes	yes	no	yes	no
16	yes	yes	yes	yes	no	no	yes
17	no	no	no	no	yes	no	yes
18	yes	no	no	no	yes	yes	no
19	no	no	yes	no	yes	yes	no
20	yes	no	yes	no	yes	no	yes
21	no	no	no	yes	yes	no	no
22	yes	no	no	yes	yes	yes	yes
23	no	no	yes	yes	yes	yes	yes
24	yes	no	yes	yes	yes	no	no
25	no	yes	no	no	yes	yes	no
26	yes	yes	no	no	yes	no	yes
27	no	yes	yes	no	yes	no	yes
28	yes	yes	yes	no	yes	yes	no
29	no	yes	no	yes	yes	yes	yes
30	yes	yes	no	yes	yes	no	no
31	no	yes	yes	yes	yes	no	no
32	yes	yes	yes	yes	yes	yes	yes

*Note*: Every factor occurs an equal number of times at high and low levels (i.e. balanced) and all factors are orthogonal to each other. Each effect estimate involves all 32 of the conditions in Table 1, thereby maintaining the power associated with all participants. This Resolution IV design means that all main effects are aliased with 3-way and higher interactions, and all 2-way interactions are aliased with 2-way and higher interactions, on assumption that non-negligible 3-way interactions are unlikely. In contrast, a standard RCT is aliased for all main effects and interactions of treatment components

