## Methods

### Study design

A single centre, stratified (moderate depression, operationalized as PHQ-9 score < 20; severe depression, operationalized as PHQ-9 score > =20; source of recruitment: directly from the internet versus within an National Health Service Improving Access to Psychological Therapies (IAPT) treatment service; antidepressant use: none versus at a recommended clinical dose), block randomized, single-blind, fractional factorial trial, based in England will be conducted on the internet, randomized at the level of the patient. It will be a full scale internet-delivered component selection experiment with seven experimental factors evaluated, each at two levels ((presence, coded as +1 versus absence, coded as -1 of component; in other words, effect coded), using a 32-condition balanced fractional factorial design (2_IV_
^7-2^)). This design will allow the estimation of all main effects and several pre-specified 2-factor interactions among the seven intervention factors; in statistical terminology, a Resolution IV design because main effects are aliased with 3-way interactions. Table 1 describes the specific combinations of 2-level intervention factors in the experimental design. A full factorial design of seven factors would have required 2^7^ = 128 conditions; the fractional factorial design reduces the total number of conditions by three-quarters.

Within the chosen fractional factorial design, all participants will be randomized to receive at least one component of CBT and in the majority of cases 3 or 4 components of CBT. This design does not have any conditions in which participants receive no treatment components, i.e., there is not a no-treatment, treatment-as-usual, or waiting list control cell, making it suitable for use in a clinical service. Main effects and interactions are estimated based on aggregates across experimental conditions. For each main effect, half of the study population will be randomized to one level of the factor (e.g., conditions 9–16, 25–32 presence of concreteness training) and half will be randomized to the other level of the factor (e.g., conditions 1–8, 17–24 absence of concreteness training); thus, the full sample size can be used to determine each of the main effects (and interactions), making this design efficient for power and sample size.

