### Intervention component factors

The content of the program will be based on CBT for depression, programmed by the research team [https://mindresolve.minddistrict.co.uk] hosted on an established and secure internet-treatment platform provided by MindDistrict, a Dutch internet health services company. All participants will complete a welcome module which includes a mood diary and basic psychoeducation about depression prior to randomisation and then if randomised will receive between 1 to 7 treatment components depending on the randomized treatment condition.

Each module takes around an hour to complete in session and 1-to-2 weeks to practise. Each treatment component will include written psycho-education, images, written vignettes, online experiential exercises using audio-recordings with automatic feedback, downloadable audio exercises to practice skills, interactive questionnaires, video vignettes of patients explaining therapy, and response boxes in which patients write about their experiences and plans. The modules each follow the same basic structure: reflection on previous session; introduction of new technique; practical exercises and planning how to practise or implement the technique in daily life. The intervention is accessed through a secure website, with each participant having a password protected account. Participants’ log-ins will be automatically recorded by the programme, allowing for an automated measure of treatment compliance. Reminder emails will be sent to participants after two weeks if they have not completed the module. The participant can work through each module at his own pace but can only move from one module to the next once the therapist has provided feedback.

All components will involve brief prescribed therapist online support to improve retention and adherence [7], in which secure online written feedback is provided at the end of each completed module, with the option for additional secure messaging between therapist and patient. The coach will highlight any positive steps made and encourage participants to sustain these as well as pointing out areas to focus on over the next module. Participants will also be able to send questions to their assigned therapist throughout the programme if they are having difficulty with a specific exercise. Well-established self-report measures of anxious and depression symptoms (PHQ-9, GAD-7) are presented at the end of each component to assess symptom change.

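### A main effect estimates a component plus its extra supported module, so on its own it is not evidence of a specific effect beyond common factors

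*Protocol article*

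**What the plan says.** All references are to the protocol article.

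- **Aims and objectives.** For any component, the 16 conditions where it is present "are equivalent for treatment credibility, structure, delivery, rationale, therapist contact, and therapist allegiance with the aggregate of the 16 conditions where it is absent". From this the article infers: "This design therefore provides an improved psychotherapy attentional control condition able to disentangle specific from non-specific common treatment factors". It then sets a rule for interpretation: "A significant main effect for any component would be evidence for a specific treatment effect within CBT for depression beyond non-specific common therapy factors". The same section names therapist support and the giving of a rationale as examples of generic elements.
- **Study design.** Each factor has two levels: "presence, coded as +1 versus absence, coded as -1 of component". Participants receive at least one component and "in the majority of cases 3 or 4 components of CBT".
- **Intervention component factors.** Randomised participants "will receive between 1 to 7 treatment components depending on the randomized treatment condition". A module takes about an hour, followed by one to two weeks of practice, and "secure online written feedback is provided at the end of each completed module". No filler or sham module is described for an absent component.
- **Relaxation.** The description of this module shows that a module carries its own rationale.

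**The concern.** The absence aggregate can serve as an attentional control only if both sides of each comparison get the same amount of generic treatment. If absence means one module fewer with nothing in its place, the presence side also gets more therapist feedback, rationale, content and practice time. The article itself counts therapist support and rationale as generic. A non-zero main effect could then come from the technique, from the extra supported module, or from both.

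At stake is the article's secondary claim that the design separates specific from common factors. If one more supported module helps regardless of its content, an inert technique could be reported as a specific active ingredient.

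**Working it through.** **Inputs.** All 32 rows of Table 1, coded 1 for yes and 0 for no; the per-module support described in Intervention component factors; N = 632 and alpha 0.10 from Sample size calculation.

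**1. Reproduce the stated design.** Every factor is present in 16 conditions and absent in 16, and all pairwise cross-products of the effect-coded columns are 0. The number of components per condition is 1 (3 conditions), 2 (4), 3 (7), 4 (12), 5 (5) and 7 (1), with mean 3.5. Three or four components occur in 7 + 12 = 19 of 32 conditions (59%), which agrees with the stated majority. The table is as described.

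**2. Planned modules by factor level, using the article's own example (relaxation).**
- Present, conditions 17–32: 64 modules / 16 = 4.0.
- Absent, conditions 1–16: 48 modules / 16 = 3.0.

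**3. All seven factors.** By balance and orthogonality, each of the other six components appears in 8 of the 16 presence conditions and 8 of the 16 absence conditions. Both sides therefore receive 6 × 8/16 = 3.0 of the others. The presence side adds the component itself: 3.0 + 1 = 4.0. Direct counting gives 4.0 versus 3.0 for every factor. Planned written feedbacks follow the same split, 4 versus 3 on average. If the welcome module also attracts feedback (an assumption), the split is 5 versus 4. The difference is still one.

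**4. Covariate adjustment cannot help.** Let e_j be the ±1 code for component j. Module count is M = 3.5 + 0.5 × (e_1 + … + e_7), an exact linear function of the terms already in the model.

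**5. What is identified.** Write s_j for the specific effect of component j and g for a generic gain per supported module, taken as the same for each module. The main effect of component j estimates s_j + g, not s_j. In a contrast between components, g cancels. Component j against the mean of the other six estimates s_j minus the mean of the other six s values. Its SE is sqrt(1 + 1/6) = sqrt(7/6) = 1.08 times that of a main effect.

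**6. Illustration only.** The documents give no value for g. With 316 per level, the noncentrality for an inert technique (s_j = 0) is g × sqrt(632/4) = g × sqrt(158) = 12.57 g, with g in SD units. Two-sided rejection at alpha 0.10 (critical value 1.645):

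| g per module (assumed) | Noncentrality | Rejection probability |
|---|---|---|
| 0 SD | 0 | 10% |
| 0.05 SD | 0.63 | about 17% |
| 0.1 SD | 1.26 | about 35% |

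**The case against.** The strongest reply is that nothing in the primary analysis depends on the disputed sentences. The primary aim is to test main effects and selected interactions, and specific-versus-common factors is offered as a further advantage. **This stands.** A reader might infer that the main effects are biased or that component selection is compromised. The documents do not support that: each main effect is a valid randomised estimate of adding the component as delivered.

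A reader might also infer that the plan never examines specificity. **That would be wrong.** Aims and objectives, Follow-up assessments and outcome measures, and Mediation and moderation analysis together plan mechanism measures matched to components and tests of mediation. These bear on specificity, but they do not rescue the rule that a significant main effect is enough.

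Three further points stand:

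- The abstract's aim to "determine the main effect of each treatment component and its relative efficacy" is not at fault. Seven orthogonal effects on one scale can be compared, and that sentence makes no claim of specificity.
- A shared generic gain would raise all seven effects together. The article predicts that many effects will be insignificant, and near-zero effects for some components would limit how large such a gain could be.
- Similar delivery mode and therapist allegiance are plausible, given one platform, scripted feedback and trained therapists. The equivalence fails on amount, not on every listed attribute.

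It is also tempting to compound the 35% over seven components: 1 − 0.65^7 = 95% for at least one false finding. That rests on an assumed gain, and with no generic gain the same calculation already gives 1 − 0.90^7 = 52%. It should not be used to size this point.

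**Conclusion.** The point holds as an error of statement and inference. Equivalence in therapist contact and rationale is wrong as to amount: each presence aggregate is planned to receive on average one more supported module (4.0 versus 3.0), and only the other six components are balanced. The rule that a significant main effect alone is evidence of a specific effect therefore does not follow, and adjusting for module count cannot repair it.

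The difference is in planned average exposure. Individual conditions overlap (2 to 7 components with relaxation, 1 to 5 without), and completed modules may differ from planned ones. The finding should not be read as 33% more treatment received. How often an inert technique would be called active cannot be stated from the documents; the 10% to 35% range only illustrates assumed gains of 0 to 0.1 SD per module. The module-count result needs no such assumption.

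**What to change.** 1. Restrict the equivalence statement in Aims and objectives to the other six components and to qualitative features such as delivery mode and therapist allegiance.
2. Withdraw the sentence that a significant main effect alone is evidence of a specific effect, and qualify the attentional-control claim to match.
3. Describe each main effect as the effect of adding that module with its support. Keep its test against zero for component selection.
4. Base any specificity statement on the planned mechanism and mediation analyses. Supplement them with a pre-specified 6-df test that the seven main effects are equal, followed by between-component contrasts.
5. State the limits of those contrasts. They show differential effects only, would be null if all seven components had equal specific effects, and assume the same generic gain for each module.

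The cost is a text change and extra contrasts from the same fitted model. For each component against the mean of the other six, the SE is about 8% larger than for a main effect. At N = 632 and alpha 0.10, power for a 0.2 SD difference is about 75%, against 81% for a main effect of that size. No change to the design, the interventions or the sample size is needed.
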